## Abstract

**Objective::**

This manuscript describes the protocol of an investigator-initiated, international, multicenter, long-term, prospective observational study named PRactice of VENTilation in PEDiatric Patients (PRoVENT-PED), designed to investigate the epidemiology, respiratory support practices and outcomes of critically ill pediatric patients.

**Design::**

Data will be collected biannually over 10 years during predefined 4-week intervals, with an additional optional period to accommodate data collection during an epidemic or pandemic. The specific focus of PRoVENT-PED will evolve as the study progresses, initially emphasizing collecting detailed ventilator data from invasively ventilated patients. In later phases, the focus will shift to noninvasive respiratory support and typical aspects of respiratory support, like patient-ventilator asynchronies, weaning practices, and rescue therapies, as extracorporeal support. PRoVENT-PED includes patients under 18 years of age, admitted to a participating intensive care unit, and receiving respiratory support. The endpoints vary with the focus in each phase but will always include a set of key settings and ventilation parameters and related outcomes. If applicable, potentially modifiable factors and associations with outcomes will be studied. The pilot feasibility study demonstrated that the electronic capturing system effectively collects all necessary data within a reasonable time limit, with little missing data.

**Conclusion::**

PRoVENT-PED is a 10-year, international, multicenter study focused on collecting data on respiratory support practices in critically ill pediatric patients. Its scope evolves from invasive to noninvasive ventilatory support, ultimately encompassing patient-ventilator asynchronies, weaning practices, and rescue therapies.

## INTRODUCTION

Critically ill patients often require respiratory support,^(1)^ frequently involving invasive or noninvasive ventilation. Numerous studies in adult patients have shown significant variation in respiratory support practices, which have evolved.^(2-5)^ These studies informed clinical trials that ultimately transformed care for critically ill adults, improving outcomes through evidence-based adjustments - for instance, in ventilator settings, noninvasive support strategies, and other respiratory support practices, enhancing patient outcomes.^(6-14)^

The need for respiratory support is similarly prevalent among critically ill children. However, research in pediatric populations remains scarce, leading to, amongst others, a reliance on data from adult studies to guide pediatric respiratory support practices.^(15,16)^ This reliance may be misguided, as physiological differences, including lung and thorax compliances, susceptibility to ventilator-induced lung injury (VILI),^(17)^ and age-related differential responses to pulmonary injury^(18,19)^ and oxygen toxicity,^(20,21)^ suggest that adult findings may not translate directly to pediatric patients.

We designed a long-term, prospective observational study, named PRactice of VENTilation in PEDiatric Patients (PRoVENT-PED) focused on collecting comprehensive data on respiratory care practices in critically ill pediatric patients. The study employs an adaptive design, allowing its scope to evolve over the 10 years. Initially, it will prioritize collecting detailed ventilator data from invasively ventilated patients. In later phases, the scope will shift to various noninvasive respiratory support and more specific aspects of invasive ventilation. The feasibility of PRoVENT-PED was rigorously tested in two Dutch hospitals to confirm its suitability for broader implementation.

## METHODS

### Design and ethics

PRoVENT-PED is an investigator-initiated, long-term, prospective, international, multicenter study that will collect detailed respiratory support data biannually over 10 years during predefined 4-week intervals, with an optional additional period to accommodate data collection during epidemics or pandemics. International and regional networks of pediatric intensivists and respiratory therapists are responsible for recruiting participating centers. Study coordinators guide national and regional coordinators in acquiring ethical approval, and help in the administrative processes. Due to its observational nature, participation may not require individual patient consent in most nations or regions; however, this depends on national and regional legislation, and local policies of the participating centers. The study protocol was initially approved by the Institutional Review Board of the University Medical Center Groningen, the Netherlands (METc 2023/375). PRoVENT-PED is registered at Clinicaltrials.gov (study identifier NCT06220825). PRoVENT-PED complies with the International Conference on Harmonization-Good Clinical Practice (ICH-GCP).

### Adaptive study

PRoVENT-PED employs an adaptive design, allowing the study's scope to evolve over the years the study is conducted (Figure 1). Initially, the study will prioritize the collection of comprehensive and detailed ventilator data from patients who are receiving invasive ventilation, as outlined in the following sections. The scope of each successive phase will be thoroughly outlined in a study amendment and documented on Clinicaltrials.gov to ensure transparency and provide ongoing updates on the study's evolving objectives.

**Figure 1 f1:**
[figure not shown]
The schematic presentation of PRoVENT-PED highlights its adaptive design.

### Patients

Overall, patients are eligible for participation in PRoVENT-PED if: (1) under 18 years of age; (2) admitted to the ICU of a participating hospital during the period of data collection; and (3) receiving respiratory support for at least 12 hours, which ranges from simple supplementary oxygen or high-flow nasal oxygen (HFNO) to noninvasive ventilation and invasive ventilation, with or without extracorporeal membrane oxygenation (ECMO). During each phase, the study's evolving focus will adapt the inclusion criteria. In the initial phase, with the emphasis on invasive ventilation, receiving invasive ventilation will serve as an additional inclusion criterion. In the subsequent phases, the focus will shift to noninvasive respiratory support, accompanied by revised inclusion criteria that reflect this change in emphasis.

Preterm infants, i.e., patients with a postconceptional age corrected for gestational age below 40 weeks, are excluded from participation. Naturally, with each shift in focus, the exclusion criteria will also change during each phase. For example, if the study's emphasis transitions to noninvasive ventilatory support, patients who are receiving only invasive ventilation will be excluded from participation.

### Data collection

All data to be collected are part of standard clinical care. Throughout each phase of the study, the data collected will be tailored to align with the evolving focus of the research, ensuring that it remains relevant and reflects the specific objectives of each stage. At admission, we will collect data on patient demographics - including age, gestational age, sex, height and weight, comorbidities, and baseline characteristics - including reasons for intensive care unit (ICU) admission, and the start of respiratory support, presence of the pediatric acute respiratory distress syndrome (PARDS), and disease severity scores. For 4 days, beginning with the day of start of respiratory support, daily data will be collected at a time in the morning - including data on respiratory support and the respiratory status. Follow-up will be until day 28 to collect outcome data, including the date of stop of respiratory support, date of ICU discharge, and life status at ICU discharge or at day 28, whichever comes first.

Investigators will transcribe all collected data into a web-based electronic Case Report Form (eCRF) (Castor Electronic Data Capture, Amsterdam, the Netherlands).^(22)^ The eCRF complies with all applicable laws and regulations. Transcription will only take place in a secure environment. Directly identifying personal data will be separated from the research data and replaced by an assigned code. The directly identifying data will only be used to contact the patients and will only be available to the local investigators. Access to the assigned codes linked with personal data will be password-protected, restricting access to only the data directly related to the local investigator.

### Study endpoints

The study endpoints vary based on the study's evolving scope. Since the scope of the initial phase of PRoVENT-PED is invasive ventilation, key endpoints include a set of ventilator settings and ventilation parameters, such as tidal volume (V_T_); maximum (Pmax), peak (Ppeak), plateau (Pplat) and mean airway pressures (Pmean); positive end-expiratory pressure (PEEP); fraction of inspired oxygen (FiO^2^); and respiratory rate (RR) at fixed time points over the first four days of invasive ventilation. Driving pressure (ΔP), respiratory system compliance (C_RS_), and measures of ventilation intensity are calculated daily from these data. Other endpoints include duration of ventilation in survivors and nonsurvivors, the number of days free from invasive ventilation and alive at day 28, length of stay in ICU and hospital, and mortality rates in ICU and hospital and at day 28.

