### Definitions

Day 0 of invasive ventilation is defined as the day respiratory support is started in the participating ICU; in the initial phase, this is the day at which invasive ventilation is started. Day 1 is defined as the first full calendar day, with Day 2 and Day 3 representing the two consecutive mornings that follow. Pediatric acute respiratory distress syndrome is defined according to the 2023 Pediatric Acute Lung Injury Consensus Conference (PALICC-2) definition.^(23)^ Intensive care unit length of stay is defined as the time between ICU admission and discharge or death; duration of respiratory support, in the initial phase invasive ventilation, is defined as the time between initiation and successful liberation. Intensive care unit mortality is defined as any death until ICU discharge or day 28, whichever comes first.

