### Calculations

Ventilator-free days at day 28 (VFD-28) is calculated as 28 minus the number of days a subject was successfully liberated from ventilation after initiation. If a patient dies within 28 days, VFD-28 will be recorded as zero. The V^T^ is normalized to actual body weight (ABW), and ΔP,^(8)^ C_RS_,^(24)^ mechanical power (MP)^(25)^ and mechanical energy (ME) of ventilation,^(26)^ are calculated using the following equations 1 to 9:

[Equation 1]
$${\text{V}}_{\text{T}}\text{normalized to ABW}={\text{V}}_{\text{T}}/\text{ABW}$$

[Equation 2]
ΔP=Pplat−PEEP in volume-controlled ventilation (VCV)

[Equation 3]
ΔP=Pmax−PEEP in pressure-controlled ventilation(PCV)

[Equation 4]
$${\text{C}}_{\text{RS}}={\text{V}}_{\text{T}}/(\text{Pplat}-\text{PEEP})(\text{with VCV})$$

[Equation 5]
$${\text{C}}_{\text{RS}}={\text{V}}_{\text{T}}/(\text{Pmax}-\text{PEEP})\text{(with PCV)}$$

[Equation 6]
$$\text{MP}=0.098^{*}\;{\text{V}}_{\text{T}}*\text{RR}*(\text{Ppeak}-0.5^{*}\Delta \text{P})(\text{with VCV})$$

[Equation 7]
$$\text{MP}=0.098^{*}\;{\text{V}}_{\text{T}}*\text{RR}*(\mathrm{Pmax}-0.5^{*}\Delta \text{P})(\text{with PCV})$$

[Equation 8]
$$\text{ME}=0.098^{*}\;{\text{V}}_{\text{T}}/{\text{kg}}^{*}(\text{Ppeak}-0.5^{*}\Delta \text{P})$$

[Equation 9]
$$\text{ME}=0.098^{*}{\text{V}}_{\text{T}}/{\text{kg}}^{*}(\mathrm{Pmax}-0.5^{*}\Delta \text{P})$$

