## RESULTS

Of 398 patients screened, 125 were eligible for this pilot study, 91 from the UMCG and 34 from the AUMC (Figure 1S - Supplementary Material). The main reason for exclusion was not receiving invasive ventilatory ventilation. Patients were predominantly male, and most patients were neonates or infants (Table 1). The most common comorbidities were pulmonary diseases, syndromes, and genetic abnormalities. Most patients were admitted to the ICU and intubated due to pulmonary conditions, and 11% met PARDS criteria. All-cause 28-day ICU mortality was 8%, the median duration of ventilation was 4 [2 - 10] days, and the median length of ICU stay was 5 [3 - 11] days.

**Table 1 t1:** Patient demographics, baseline characteristics and outcomes

Variables		
Patient demographics		
	Age (months)	8 [2 - 72]
	Sex (male)	80 (64)
	Body weight (kg)	8 [5 - 22]
	Body height (cm)	74 [55 - 120]
	Premature birth	14 (11)
Disease severity score		
	PIM III	1 [0 - 2]
Medical history		
	Pulmonary	26 (22)
	Cardiac	23 (18)
	Neuromuscular	5 (4)
	Syndrome or genetic abnormalities	32 (26)
	Oncologic	1 (1)
	Organ transplant	8 (7)
	Chronic ventilation	2 (2)
	Mental retardation	6 (5)
Reason for ICU admission		
	Respiratory	70 (57)
	Cardiac	8 (7)
	Neuromuscular	4 (3)
	Postoperative	32 (26)
	Home ventilation	1 (2)
	Renal failure	3 (2)
	Trauma	6 (5)
	Intoxication	1 (1)
Main reason for invasive ventilation		
	Respiratory	65 (52)
	Circulatory	13 (10)
	Neurological	9 (7)
	Metabolic	1 (1)
	Postoperative weaning	33 (26)
	Trauma	4 (3)
Barotrauma during admission		
	Pneumothorax	3 (3)
	Subcutaneous emphysema	1 (1)
	Pneumomediastinum	1 (1)
Tracheostomy		3 (2)
Discharged		106 (85)
Destination of discharge		
	ICU of another hospital	5 (4)
	Ward	91 (72)
	Other healthcare facility	6 (5)
	Home	4 (3)
Duration of ventilation (days)		4 [2 - 10]
Length of ICU stay (days)		5 [3 - 11]
28-day mortality		10 (8)

PIM III - Pediatric Index of Mortality III; ICU - intensive care unit. Data presented as median with interquartile range [25^th^ - 75th quartile] or n (%).

Median time to collect all data per patient was 20 [15 - 25] minutes (Table 1S - Supplementary Material), the amount of missing data was low (Table 2S - Supplementary Material) and considered acceptable, and local investigators expressed no difficulties using Castor EDC as eCRF for data entry.

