PRoVENT-PED has several limitations. Selection bias may occur as centers interested in various types of ventilatory support are more likely to participate. We will invite ICUs through various organizations and networks to reduce this risk. Furthermore, since the study is unfunded, resource-rich ICUs may be overrepresented. We will attempt to mitigate this by offering full support to participating centers where feasible. Data collection could be challenging due to the involvement of ICUs across different countries, each with varying health record systems and spanning both resource-rich and resource-limited settings. To address this, we will streamline respiratory support data and limit follow-up to either ICU discharge with a maximum of 28 days, aiming to make the workload manageable for all participating centers.

Additionally, some patients may be lost to follow-up due to transfers from participating to non-participating centers. Finally, given its observational design, PRoVENT-PED can identify associations between practice and outcomes but cannot establish causality. Nevertheless, these associations will inform the design of future randomized clinical trials.

In conclusion, PRoVENT-PED is a well-scaled, long-term observational study with an adaptive, global design. This design enables the collection of extensive data across diverse patient populations and settings. This study will provide valuable insights that can enhance and guide respiratory care for critically ill pediatric patients.

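### Vital status is followed only to ICU discharge or day 28, yet hospital stay, hospital mortality and day-28 mortality are listed as endpoints distinct from ICU mortality

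*Protocol article*

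**What the plan says.** All references are to the protocol article.

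- **Study endpoints**, among the items introduced as other endpoints: "length of stay in ICU and hospital, and mortality rates in ICU and hospital and at day 28". ICU, hospital and day-28 mortality appear as three separate outcomes.
- **Data collection** begins broadly: "Follow-up will be until day 28 to collect outcome data". It then fixes vital status as "life status at ICU discharge or at day 28, whichever comes first". The outcome dates it names are the end of respiratory support and ICU discharge. It names no hospital discharge date or hospital vital status.
- **Definitions**: "Intensive care unit mortality is defined as any death until ICU discharge or day 28, whichever comes first". No hospital outcome is defined.
- **Calculations**: "If a patient dies within 28 days, VFD-28 will be recorded as zero". This rule does not depend on where the death occurs.
- **Discussion**, on limitations: to keep the workload manageable, the study will "limit follow-up to either ICU discharge with a maximum of 28 days".

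**The concern.** The endpoint list needs information from after ICU discharge, and the follow-up rule stops at ICU discharge. If both are applied as written, a child who leaves the ICU alive and dies on the ward before day 28 counts as a survivor in a figure labelled day-28 mortality, and keeps a positive VFD-28 where the Calculations section requires zero. Hospital mortality and hospital stay cannot be derived for children who leave the ICU for a ward.

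The label matters because the Discussion promises to explore geo-economic differences and their effect on outcome. Discharge and transfer practice could plausibly differ between such settings. A figure truncated at ICU discharge but labelled day 28 could then mix differences in discharge practice with differences in survival. The article gives no figure for this, so it is a possible consequence and not a demonstrated one.

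**Working it through.** **1. The two mortality outcomes under the stated rule.** ICU mortality is death up to the earlier of ICU discharge and day 28 (Definitions). Vital status is recorded at the earlier of ICU discharge and day 28 (Data collection). A day-28 mortality built from that field counts the same deaths, so the two endpoints coincide. The pilot shows this already. The Results text gives 8% as all-cause 28-day ICU mortality, and Table 1 gives 10 (8%) as 28-day mortality. Both labels cover the same 10 deaths.

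**2. Pilot inputs (Results and Table 1).** "Of 398 patients screened, 125 were eligible for this pilot study". Discharged: 106. Destinations: another hospital's ICU 5, ward 91, other healthcare facility 6, home 4. Deaths: 10. Also, "the median length of ICU stay was 5 [3 - 11] days".

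**3. Reproducing the pilot's own figures.**
- Discharged: 106/125 = 84.8%, printed as 85%.
- Destinations: 5 + 91 + 6 + 4 = 106, which agrees.
- Deaths: 10/125 = 8.0%, which agrees.

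**4. Day-28 status.** Under the rule, observation of the 106 discharged children (85%) ends at ICU discharge. The upper quartile of ICU stay is 11 days, so most stays ended well before day 28. Status at day 28 is known for the 10 deaths. It is also known for the remaining 125 − 106 − 10 = 9 children if they were still in the ICU at day 28, which Table 1 does not state. At most that makes 19/125 = 15%.

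**5. Hospital outcome among discharged children.** The 4 sent home had left hospital, so their hospital outcome is complete.
- Open for at most 106 − 4 = 102, and 102/125 = 82%.
- If transfer to another hospital or facility also ends the index hospital stay, only the 91 ward transfers remain open, and 91/125 = 72.8%, or 73% (Table 1 prints 72).

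**6. What the pilot table contains.** The pilot followed the initial-phase data plan (Feasibility study, Data collected). Table 1 reports ICU stay and discharge destination, but neither hospital stay nor hospital mortality.

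**7. Possible size of the error (assumption, not in the article).** Suppose 0.5% to 3% of discharged children die between ICU discharge and day 28, and take the pilot's discharge share of 0.848.
- Missed deaths per 3,000 patients: 3,000 × 0.848 × 0.005 = 13, up to 3,000 × 0.848 × 0.03 = 76.
- True day-28 mortality against a recorded 8.0%: 8.0% + 0.848 × 0.5% = 8.4%, up to 8.0% + 0.848 × 3% = 10.5%.
- Mean VFD-28 overstated, crediting 28 − 4 = 24 days per missed death (4 being the median days of ventilation): 0.848 × 0.005 × 24 = 0.1 days, up to 0.848 × 0.03 × 24 = 0.6 days.

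These values show scale only. Re-ventilation after ICU discharge is not included.

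**The case against.** The strongest reply is that the article condenses a fuller protocol. Data collection opens with follow-up to day 28 and introduces its list of outcome data as inclusive, so the case report form may hold fields that the article does not name. This stands in part. A reader might infer that hospital data are not collected at all, and the article does not prove that. It does not remove the conflict, because the vital-status clause and the Discussion both state the shorter window explicitly, and the Discussion gives a reason for it.

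Other stronger readings are also unsupported:

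- **That the main analysis is undermined.** The sample size and the smoothed association curves use ICU mortality, and the univariate analysis uses 28-day ICU mortality. Both fit the observed window.
- **That hospital outcome is unknown for 85%.** That share applies to day-28 status. For hospital outcome the share is at most 82% among discharged children, because 4 went home.
- **That nine children were still in the ICU at day 28.** Table 1 does not describe them. Some of its percentages do not fit a denominator of 125 (26 is shown as 22%, 70 as 57%), so incomplete records are possible.
- **That VFD-28 fails for most patients.** The date respiratory support stopped is collected. The value is wrong only after a death or re-ventilation between ICU discharge and day 28, although it cannot be verified for the 85% discharged.
- **That the uncapped definition of ICU stay is an error.** Observation ending at day 28 is ordinary censoring, and time-to-event methods are planned.

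The Discussion also discloses the limited follow-up and loss through transfers. It does not say that this leaves some listed endpoints unobserved.

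**Conclusion.** The contradiction holds and should be fixed. Under the stated follow-up rule, day-28 mortality adds nothing to ICU mortality truncated at day 28, hospital mortality and hospital stay have no named data behind them, and the death rule in VFD-28 cannot be checked after ICU discharge. On the pilot's figures this leaves day-28 status unobserved for 106/125 (85%), and hospital outcome open for between 91/125 (73%) and 102/125 (82%) among discharged children. These shares assume that the pilot's discharged children left the ICU before day 28 and that no fields beyond those named were collected.

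The number of wrong values is a different and smaller quantity. It depends on deaths and re-ventilation after ICU discharge, for which the article gives no rate. The harm is confined to endpoints listed as other endpoints and to the labelling of mortality.

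**What to change.** Reconcile Study endpoints, Data collection, Calculations and the follow-up statement in the Discussion, by one of two routes.

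**Route A, wording only.** Delete hospital mortality and hospital length of stay. Replace day-28 mortality throughout, including the pilot table, with ICU mortality truncated at day 28. State in Calculations that VFD-28 assumes that children discharged alive and off the ventilator remain so to day 28. This adds no data collection.

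**Route B, if the endpoints are wanted.** Collect vital status at day 28, and hospital discharge date and status, for every child. Amend Data collection and the Discussion to match. Discharged and transferred children would have to be traced, and hospital discharge may fall after day 28. The article gives no basis for costing this work, and it runs against the stated aim of a manageable workload in an unfunded study. Re-ventilation after ICU discharge would stay unobserved unless it too is recorded, so the VFD-28 assumption would still need stating for that part.

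The choice should be made before further data collection, because post-ICU status that is not recorded prospectively may be hard to recover.
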